#### 2.3.3. Transthoracic Echocardiogram (TTE)

A TTE will be performed in all patients at baseline, 3, 6, 12, and 24 months (Supplementary Table S1). A comprehensive evaluation of the systolic and diastolic function, ventricular and atrial geometry, will be performed following the guidelines by the American Society of Echocardiography on a Vivid E95 ultrasound system (GE Healthcare, Horten, Norway) [40]. Special attention will be given to acquiring a 3D measurement of the left ventricular ejection fraction (LVEF) and performing deformation imaging of the left ventricle global longitudinal strain (GLS). The right ventricular function will be evaluated by tricuspid annular plane systolic excursion (TAPSE) and peak systolic velocity S’ derived from color coded tissue Doppler imaging (TDI). Diastolic dysfunction will be based on an average E/e′ ratio > 15 and a LA area > 30 cm^2^.

#### 2.3.4. Computed Tomography (CT) Scan for Calcium Scoring

A CT-scan will be performed at baseline, 12 months, and 24 months in order to detect calcium deposits in the coronary arteries of the heart (Supplementary Table S1). A higher coronary calcium score suggests a higher chance of significant narrowing in the coronary arteries.

#### 2.3.5. Blood Sampling

Blood samples of all participants will be collected at baseline (immune baseline, four tubes i.e., serum, EDTA, fluoride, and one EDTA tube on ice) and before each ICI cycle (immune follow-up, three tubes i.e., serum, EDTA, and fluoride) (Supplementary Table S2). One additional blood sample (serum) will be taken at baseline, 3, 6, 12, and 24 months at the same time of routine laboratory testing.

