Cardiac markers such as high-sensitivity troponin I/T (hs-TnI/hs-TnT), BNP, and NT-proBNP are crucial in the diagnosis of CV diseases. For example, troponin is a well-known cardiac biomarker that has become indispensable in the diagnosis of acute coronary syndromes. However, its role in cardio-oncology, more specifically in the active surveillance of ICI-mediated CV events, is not clear. Hence, the current guidelines are based on anecdotal evidence and expert opinions, due to the lack of solid data and prospective studies [33,37]. Therefore, cardiac monitoring, in patients receiving ICIs, is not always implemented by oncologists, as many questions remain unanswered:How should hs-TnI/hs-TnT levels be graded? The Common Terminology Criteria for Adverse Events (CTCAE, Version 5) is widely accepted as the standard classification and severity grading scale for adverse events in cancer therapy, clinical trials, and other oncology settings [38]. However, the current grading system makes it challenging to accurately document and report the severity and incidence of increased cardiac troponins, leading to ICI-induced CV toxicity. Furthermore, BNP and NT-proBNP are not even listed in the current CTCAE criteria.What are the cut-off values for cardiac markers for clinically meaningful changes in ICI-treated patients? When do further investigations need to be performed? (The upper limit of normal (ULN) is determined on a healthy patient population).What is the appropriate time interval between the testing of cardiac markers?What is the appropriate monitoring duration of cardiac markers? Three months or longer?

Our narrative review summarized previously conducted research regarding troponin levels in patients receiving ICI [39]. As prospective data are lacking, we initiated a multicenter, prospective trial (NCT05699915) in which patients with a solid tumor eligible for ICI treatment, i.e., anti-CTLA-4, anti-PD-1, and/or anti-PD-L1, will be enrolled. Patients receiving concurrent systemic antineoplastic treatment will be excluded in order to have a homogeneous treatment population. The patients included in this study will receive a thorough CV work-up at baseline and at regular time points during treatment for a total period of two years. Our aim is to study cardiac markers in patients receiving ICI therapy and to explore the association between CV abnormalities and major adverse cardiac events (MACEs).

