#### 2.4.1. Primary Endpoint

The incidence of an elevated hs-TnT above the ULN if the baseline value was normal; or 1.5 ≥ times baseline if the baseline value was above the ULN within the first three months of treatment. The maximum measured value will be taken into account *.

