### 2.6. Data Analysis

All patient data will be collected via REDCap (a Research Electronic Data Capture), a secure HIPAA (Health Information Portability and Accountability Act)-compliant Web-based application, using a standardized data collection form. Data needed for analyses will be extracted from REDCap [43,44]. For categorical variables, frequencies and percentages will be reported. Where values are missing, percentages will be calculated for the available cases, and the denominator will be mentioned. Continuous variables will be summarized as mean with standard deviation and range.

For the primary endpoint, the cumulative incidence of troponin elevation will be calculated with death as a competing risk. Cumulative incidences and corresponding 95% confidence intervals will be reported at 3, 6, 12, and 24 months and a cumulative incidence plot will be used to visualize the results.

Similarly, for the secondary endpoints elevation of NT-proBNP, CV abnormalities, and MACE, cumulative incidences and 95% confidence intervals will be calculated, considering death as a competing event.

Evolution of troponin, NT-proBNP, transthoracic echocardiographic, and electrocardiographic parameters over time will be first studied in a linear mixed effects model with a random intercept per subject to account for the correlation of measurements coming from the same individual. This model will be extended with patient and treatment characteristics and their interaction with time, to evaluate their impact on the evolution of these parameters.

The association between the longitudinal evolution of troponin levels and time-to-event endpoints (CV abnormality, MACE) will be studied in a joint model combining a linear mixed model for troponin and a sub-distributional proportional hazards model for the time-to-event taking into account death as a competing event for CV abnormality and MACE. Latent random variables and common covariates are used to link the sub-models for the longitudinal measurements with the competing risk failure time data. In this way, the association between the evolution of the longitudinal measurements and time to event can be evaluated. Furthermore, by modelling the time to event, the analysis of the longitudinal measurements is adjusted for non-ignorable missing data due to informative dropout caused by deaths.

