Agreement between hs-TnT and hs-TnI (measured in all patients at baseline, 3, 6, 12, and 24 months) will be assessed in Bland–Altman curves and intraclass correlation coefficient (ICC) based on a two-way mixed effects model. The ICC and 95% confidence interval will be reported. Statistical analyses will be performed using R Software version 4.1.2 or higher.

As our clinical trial is an exploratory trial, secondary outcomes will be treated as exploratory results. Therefore, any definite finding for secondary outcomes will require further confirmatory studies to support possible findings. Hence, it is not needed to adjust for multiple testing for multiple secondary outcomes [45].

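### If troponin elevations are transient, thinner sampling after ICI stops can flatten the pooled 6–24-month cumulative incidence, which cannot by itself inform monitoring duration

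*Protocol article*

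**What the plan says.** Four parts of the protocol article bear on this point.

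- **Sampling (Section 2.3.5).** After baseline, blood is drawn "before each ICI cycle (immune follow-up, three tubes i.e., serum, EDTA, and fluoride". Separately, "One additional blood sample (serum) will be taken at baseline, 3, 6, 12, and 24 months at the same time of routine laboratory testing". Section 2.6 adds that hs-TnT and hs-TnI are "measured in all patients at baseline, 3, 6, 12, and 24 months".
- **Endpoint (Section 2.4.1).** Elevation means hs-TnT above the ULN for a patient with a normal baseline, or a 1.5-fold rise for a patient already above it. "The maximum measured value will be taken into account".
- **Analysis (Section 2.6).** "the cumulative incidence of troponin elevation will be calculated with death as a competing risk", and "Cumulative incidences and corresponding 95% confidence intervals will be reported at 3, 6, 12, and 24 months", with a single plot. End of ICI is not mentioned.
- **Motivation (Section 1).** The open questions that lead up to the trial include "What is the appropriate monitoring duration of cardiac markers? Three months or longer".

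**The concern.** A patient on ICI is sampled at every cycle. Once ICI stops, the article's text leaves that patient with only the remaining fixed samples. Because the endpoint takes the highest value seen, a short elevation counts only if a sample falls within it. In the pooled curve, the share of patients under dense sampling falls over time as patients come off ICI. Treating death as a competing event does not correct for this.

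The later part of the curve can therefore level off even if the underlying risk does not. That error would favour the conclusion that troponin need not be followed for long, which is one of the questions the Introduction raises. The authors accept the principle: in the Discussion they fault another prospective study because testing at every second cycle may have missed events.

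**Working it through.** **The plan's own figure.** Section 2.5 gives 249 patients for a 95% interval of full width 7.5 points around a 3-month incidence of 10%, raised to 276. The Wilson interval gives 249 exactly. For 10% dropout, 249/0.9 ≈ 277 and 249 × 1.10 ≈ 274. The sample size is not in dispute; the 7.5-point width serves below as a yardstick.

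**Inputs not in the documents (assumed).** Cycle length, duration of an elevation, and time on ICI. I read the per-cycle samples as including hs-TnT.

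**Step 1: number of samples.** From month 3 to month 24, a patient off ICI has 3 scheduled samples (months 6, 12, 24). Those 21 months are about 91 weeks, so a patient still on 3-weekly cycles has about 91/3 ≈ 30 (about 45 with 2-week cycles, 15 with 6-week cycles).

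**Step 2: detection of one elevation.** For an elevation of L weeks starting at random within a gap of G weeks, the detection probability is min(1, L/G).

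| Gap | L = 3 weeks | L = 6 weeks |
|---|---|---|
| 3 weeks (on ICI) | 100% | 100% |
| 4 weeks (on ICI) | 75% | 100% |
| 13 weeks (months 3–6, off ICI) | 3/13 = 23% | 6/13 = 46% |
| 26 weeks (months 6–12, off ICI) | 3/26 = 12% | 6/26 = 23% |
| 52 weeks (months 12–24, off ICI) | 3/52 = 6% | 6/52 = 12% |

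Against 3-weekly cycles, the shortfall is about 2- to 4-fold in the 13-week gap, 4- to 9-fold in the 26-week gap and 9- to 17-fold in the 52-week gap. These figures compare one off-ICI patient with one on-ICI patient. They do not measure the distortion of the cohort curve.

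**Step 3: the cohort curve.** A simulation of 200,000 patients assumed constant hazards of first elevation and of death (each 10% per 3 months), one elevation per patient, 3-weekly cycles, exponential time on ICI with median 6 months, and fixed samples only after ICI stops. With equal hazards, the true cumulative incidence at t months is (1 − 0.9^(2t/3))/2, which is 9.5, 17.2, 28.5 and 40.7% at 3, 6, 12 and 24 months. The true rise from month 12 to 24 is 40.7 − 28.5 = 12.2 points.

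| Elevation lasts | Detected at 3/6/12/24 months (%) | Rise, months 12–24 | Share of 12.2 |
|---|---|---|---|
| 0.5 month | 6.2 / 10.3 / 13.8 / 15.4 | 1.6 | 13% |
| 1 month | 8.5 / 14.1 / 19.2 / 21.5 | 2.3 | 19% |
| 2 months | 9.0 / 15.7 / 22.0 / 25.0 | 3.0 | 25% |
| Permanent | 9.3 / 16.8 / 27.4 / 37.5 | 10.1 | 83% |

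If ICI never stops, 1-month elevations give 9.4 / 16.9 / 28.1 / 40.3%, a late rise of 12.2 points, so the loss in that row comes from stopping ICI. Half-month elevations are partly missed even on 3-weekly cycles: with no stopping, the late rise is 30.5 − 21.5 = 9.0 points.

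Time on ICI matters too. With median 3 months and 1-month elevations, the late rise is 0.9 points (7%). With median 12 months and 2-month elevations, it is 5.5 points (45%).

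**Step 4: the 3-month primary estimate.** With 1-month elevations and median ICI of 6 months, 8.5% is detected against 9.4% if ICI never stops, a loss of 0.9 points. The loss is 0.8 points for half-month elevations (7.0 − 6.2) and 0.5 for 2-month ones (9.5 − 9.0). With median ICI of 3 months and 1-month elevations it is 9.4 − 7.8 = 1.6 points. All are small beside the planned 7.5-point interval width.

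**The case against.** The case on the other side has several parts.

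- **Monitoring duration is a motivating question, not an endpoint.** This stands. Sections 2.4.1 and 2.4.2 do not list it, and nowhere does the article say that the curve will settle it. Section 2.6 also calls secondary outcomes exploratory. That label, however, answers multiplicity. It does not remove a bias from estimates the plan commits to reporting.
- **Cycle-independent results are already planned.** Section 2.4.2 includes the incidence above the ULN at the fixed visits, with troponin measured in all patients. This stands, and it supplies part of the remedy. It is not the Section 2.4.1 definition, though, because a patient above the ULN at baseline counts without any rise, and it is not shown by ICI status.
- **Other models may help.** The mixed model is to include treatment characteristics and their interaction with time. The joint model addresses dropout caused by deaths. Neither qualifies the pooled incidence.
- **Material not shown could specify off-treatment sampling.** Supplementary Table S2 and the study-flow figure might do so. This stands as a limit.
- **The size rests on assumed durations.** This also stands.

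A reader might infer that the curve is bound to flatten from sampling alone, or that the trial cannot say anything about follow-up beyond three months. The documents support neither. They give no duration of elevation and no time on ICI, persistent elevations are largely picked up at the fixed visits, and those visits offer a partial answer.

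**Conclusion.** The concern holds in a limited form. As the article is written, the cumulative incidence of troponin elevation at 6, 12 and 24 months mixes risk with sampling frequency. If elevations last from half a month to two months, and median time on ICI is 6 months, the curve would show about 13–25% of a true, constant-risk rise between months 12 and 24. If elevations are permanent, it would show about 83%. The pooled curve therefore cannot by itself show whether monitoring beyond three months is needed.

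The 3-month primary estimate is only modestly affected, and the sample size is not affected. The conclusion depends on elevations being transient, on the assumed cycle length and time on ICI, and on there being no off-treatment sampling in the supplement. It is a worthwhile, inexpensive improvement to the late secondary results, not a flaw in the primary analysis.

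**What to change.** In Section 2.6:

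1. Keep the all-sample cumulative incidence for the 3-month primary endpoint.
2. For 6–24 months, add an estimate of elevation by the Section 2.4.1 definition that uses only the fixed 3-, 6-, 12- and 24-month samples, treated as interval-censored with death as a competing event.
3. Show the fixed-visit results by whether the patient is on or off ICI at the visit.
4. Base statements about late elevation or monitoring duration on items 2 and 3, not on the pooled all-sample curve.
5. Label any rate among patients still on ICI as descriptive only. Those patients are selected for not having stopped for toxicity, so their rate can fall over time for that reason.

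**Cost.** No new samples and no change to the sample size; one derived on/off-ICI variable. Fewer events will be detected, and the fixed-visit and split estimates will be less precise.

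**Limit.** Fixed visits put on- and off-ICI patients on the same schedule, but they still miss short elevations between visits, and the gaps widen from 3 to 12 months. The proportion elevated at each visit should be read beside the interval-censored estimate.

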### 2.4. Endpoints

The objective of this study is to investigate troponin and NT-proBNP values in patients receiving ICIs and their association with ICI-induced CV abnormalities and MACEs. Furthermore, we will study the calcium score, and systolic and diastolic function in this patient population. We will evaluate the associations between patient/disease characteristics/transthoracic echocardiography parameters/electrocardiography parameters and troponin/NT-proBNP levels.

#### 2.4.1. Primary Endpoint

The incidence of an elevated hs-TnT above the ULN if the baseline value was normal; or 1.5 ≥ times baseline if the baseline value was above the ULN within the first three months of treatment. The maximum measured value will be taken into account *.

#### 2.4.2. Secondary Endpoints

The incidence of hs-TnT/NT-proBNP elevations at 6, 12, and 24 months.The incidence of hs-TnT/NT-proBNP above the ULN at baseline, 3, 6, 12, and 24 months *.Evolution of hs-TnT/NT-proBNP in 24 months compared to baseline.Evolution of transthoracic echocardiography parameters at baseline, 3, 6, 12, and 24 months *.Evolution of electrocardiography parameters at baseline, 3, 6, 12, and 24 months.*Association between the evolution of troponin/NT-proBNP and transthoracic echocardiography and electrocardiography parameters at baseline, 3, 6, 12, and 24 months *.Cumulative incidence of CV abnormalities at 3, 6, 12, and 24 months based on the CARDIOTOX classification system of Sendón et al. (Table 1), with the inclusion of pericardial effusion and new arrhythmias [41]:

**Table 1 pharmaceuticals-16-00625-t001:** Cardiovascular abnormalities will be based on the CARDIOTOX classification system of Sendón et al. [41]. We will also document pericardial effusion and new arrhythmias as cardiovascular abnormalities.

Normal	Patients with Normal Biomarkers and LV Function Parameters
Mild	Asymptomatic patients with LVEF ≥ 50% with elevated biomarkers Asymptomatic patients with LVEF ≥ 50% with at least one additional abnormal echo parameter: (1) Increased LVESV (2) LA area > 30 cm^2^ (3) 10% decrease of LVEF to an LVEF < 53% (4) Average E/e’ > 14 (5) GLS > −18% (6) 15% relative reduction of GLS from baseline
Moderate	Asymptomatic patients with LVEF ≥ 40% and <50% with or without biomarker increase or other LV function abnormalities
Severe	Patients with asymptomatic LVEF < 40% Clinical HF: - HFrEF: HF symptoms/signs and LVEF < 40% - HFmrEF: symptoms/signs of HF with elevated NT-proBNP, LVEF 40–49%, and at least one additional criteria (enlarged LA, LV hypertrophy, or other relevant diastolic function parameters) - HFpEF: in presence of symptoms/signs of HF, elevated NT-proBNP, LVEF ≥ 50%, and at least one additional criteria (enlarged LA, LV hypertrophy, or other diastolic dysfunction parameters)

Abbreviations: GLS, global longitudinal strain; HF, heart failure; HFmrEF, HF with mildly-reduced ejection fraction; HFpEF, HF with preserved ejection fraction; HFrEF, HF with reduced ejection fraction; LA, left atrial; LV, left ventricular; LVEF, left ventricular ejection fraction; LVESV, left ventricular end-systolic volume; NT-proBNP, N-terminal pro-B-type natriuretic peptide.

Association between the evolution of troponin/NT-proBNP and CV abnormalities.Cumulative incidence of MACEs at 3, 6, 12, and 24 months. MACEs were defined as the composite outcomes of nonfatal stroke, nonfatal myocardial infarction, hospital admission for heart failure (HF), cardiac revascularization, and CV death.Overall survival *.Association between the evolution of troponin/NT-proBNP and MACEs.The difference in the evolution of hs-TnT/NT-proBNP/transthoracic echocardiography and electrocardiography parameters between combination therapy and monotherapy.Association between patient characteristics and troponin.Association between patient characteristics and NT-proBNP.Agreement between hs-TnT and hs-TnI levels at baseline, 3, 6, 12, and 24 months *.The proportion of severe immune-related non-CV toxicities (grades 3–5).Association between the evolution of troponin/NT-proBNP and severe immune-related non-CV toxicities (grade 3–5).Association between the evolution of troponin/NT-proBNP and overall survival.Association between the evolution of troponin and diastolic function (based on the recommendations of Nagueh et al. [42]).Association between the evolution of troponin and calcium score.

* These endpoints will also be evaluated in a preliminary analysis once 50 patients have reached their 3-month cardiac follow-up visit. The sample size was not adjusted for interim analysis as the release of preliminary results is not data-driven and does not affect the error structure of the trial. Study-level conclusions will only be made once the final results of the trial have been analyzed.

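### The CV-abnormality outcome counts elevated biomarkers as an abnormality, so its planned association with troponin and NT-proBNP evolution is partly built in

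*Protocol article*

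**What the plan says.** Section 2.4 gives the aim as studying troponin and NT-proBNP and "their association with ICI-induced CV abnormalities and MACEs".

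Section 2.4.2 defines the outcome: "Cumulative incidence of CV abnormalities at 3, 6, 12, and 24 months based on the CARDIOTOX classification system". In Table 1:

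- The Normal row is "Patients with Normal Biomarkers and LV Function Parameters".
- The first entry of the Mild row is "Asymptomatic patients with LVEF ≥ 50% with elevated biomarkers". Abnormal echo parameters are a separate, alternative entry in that row.
- In the Severe row, HFmrEF needs "symptoms/signs of HF with elevated NT-proBNP, LVEF 40–49%, and at least one additional criteria". HFpEF likewise needs elevated NT-proBNP.
- Two components outside the classification are added: "We will also document pericardial effusion and new arrhythmias as cardiovascular abnormalities".

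The same section lists as an endpoint "Association between the evolution of troponin/NT-proBNP and CV abnormalities". Section 2.6 gives the method for troponin: "The association between the longitudinal evolution of troponin levels and time-to-event endpoints (CV abnormality, MACE) will be studied in a joint model". The event part is a subdistribution hazards model with death as a competing event. The article nowhere redefines CV abnormality for this analysis.

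**The concern.** An association between a marker and an outcome is informative only if the outcome could have been judged without the marker. Here an asymptomatic patient with preserved LVEF becomes a case because the marker is raised. The Normal row also excludes anyone with a raised marker. Part of the association would therefore appear even if troponin and NT-proBNP carried no information about imaging, rhythm or clinical abnormality.

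What is at stake is the reading of one of the two associations named in the study objective. The article's Discussion hopes the results will help refine screening recommendations. A built-in association could be taken as evidence that the markers detect cardiac abnormality.

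**Working it through.** **1. The plan's own figure.** Section 2.5 assumes a 3-month incidence of troponin elevation of 10% and asks for a 95% confidence interval of total width 7.5%. The Wilson interval gives that width at n = 249, the stated number (Wald gives 246). For the 10% addition, 249 × 1.10 = 273.9 and 249/0.90 = 276.7, both close to the stated 276. The 10% is therefore a usable input, and the point does not depend on the sample size.

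**2. Overlap of predictor and outcome.**

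| Route to CV abnormality | Uses a biomarker? |
|---|---|
| Mild, first entry | Yes, alone sufficient |
| Mild, echo criteria (1)–(6) | No |
| Moderate; asymptomatic LVEF < 40%; HFrEF | No |
| HFmrEF, HFpEF | Yes, NT-proBNP required |
| Pericardial effusion, new arrhythmia | No |

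The troponin joint model is affected through the first row. The NT-proBNP association endpoint is affected through the first and fourth rows.

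**3. Illustrative size.** Let E be troponin elevation, with P(E) = e = 0.10 (Section 2.5). Let A be any abnormality by a non-biomarker route, independent of E, with P(A) = q. The documents do not give q, so a range is shown. The outcome is Y = E or A.

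- P(Y | E) = 1 and P(Y | not E) = q, so the apparent risk ratio is 1/q.
- The true risk ratio for A is q/q = 1.
- The share of cases that are biomarker-only is e(1 − q)/(e + q − eq). At q = 0.10 this is 0.09/0.19 = 47%.

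**4. Simulation under no true association.** N = 276, with a standardised marker called elevated in its top 10% and A independent of it. Y was regressed on the continuous marker by logistic regression, 1,000 runs per q, and the regression was then repeated with A alone as the outcome.

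| q | Risk ratio 1/q | Biomarker-only share | p < 0.05, outcome Y | Median OR per SD, Y | p < 0.05, outcome A |
|---|---|---|---|---|---|
| 5% | 20 | 66% | not run | not run | not run |
| 10% | 10 | 47% | 100% | 3.6 | 5.3% |
| 20% | 5 | 29% | 99.8% | 2.2 | 5.0% |
| 30% | 3.3 | 19% | 98.6% | 1.8 | 4.2% |
| 50% | 2 | 9% | 83.1% | 1.4 | 5.7% |

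Removing the biomarker route restores rejection to about 5%, with a median odds ratio of about 1.0 throughout.

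**The case against.** The strongest reply has five parts.

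- **Most routes to the outcome need no biomarker.** This is correct. A reader might infer that the association is true by definition or guaranteed. The documents do not support that: echo criteria, reduced LVEF, effusion and arrhythmia also count, and the built-in part shrinks as they become more common.
- **The planned analysis is not a risk ratio.** Also correct. Section 2.6 links a continuous troponin trajectory to a subdistribution hazard through latent variables. The figures above show direction and rough scale, and the logistic model is a simplified stand-in. A single figure such as 10 should not be read as the expected result.
- **Table 1 is loose at the edges.** It neither names the biomarkers nor sets a threshold in the Mild row, whereas the 10% follows the primary-endpoint definition. A symptomatic patient with LVEF ≥ 50% and a raised marker but no additional criterion fits no listed grade. P(Y | E) = 1 is thus an approximation. The overlap remains, because troponin and NT-proBNP are the cardiac markers under study.
- **Secondary outcomes are exploratory.** Section 2.6 uses this to justify not adjusting for multiplicity. It does not remove a shared component, and a confirmatory study with the same definition would reproduce the bias. It does limit how serious the point is.
- **Other associations are planned.** MACE, echo and ECG parameters, overall survival, diastolic function and calcium score do not use Table 1. This stands, so conclusions on the markers would not rest on this composite alone.

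**Conclusion.** The concern holds in a limited form. The association of troponin evolution with CV abnormality (the joint model in Section 2.6), and of troponin and NT-proBNP evolution with it (the endpoint in Section 2.4.2), is biased away from no association because the outcome contains the marker. Under the protocol's 10% elevation, independence, and near-certain classification of a raised marker as abnormal, the apparent risk ratio runs from 20 down to 2 for q from 5% to 50%.

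Two further inferences should be resisted. Section 2.6 does not specify a joint model for NT-proBNP: it names troponin alone, and the NT-proBNP association is only listed as an endpoint. Nor does the point undermine the trial as a whole. The primary endpoint, its analysis, the sample size and the descriptive incidence of CV abnormalities are untouched. This is a flaw in one exploratory secondary analysis that should be fixed before that analysis is run.

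**What to change.** In Sections 2.4.2 and 2.6, state that for the biomarker-association analyses only:

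1. CV abnormality means echo criteria (1)–(6) of Table 1, LVEF below 50%, clinical heart failure, pericardial effusion or new arrhythmia. The biomarker-only Mild entry does not count as an event, and non-cases are not required to have normal biomarkers.
2. For the NT-proBNP association, the heart-failure component is also derived without the NT-proBNP requirement, keeping its other elements. This is an analysis variable and does not change how a patient is graded.
3. The full CARDIOTOX classification is kept for the descriptive cumulative incidence at 3, 6, 12 and 24 months.

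The cost is some wording and derived variables from data already collected, with no change in sample size or procedures. The downside is fewer events in the joint model and hence less precision. In the illustration the events lost are the biomarker-only cases, from 66% of all cases at q = 5% to 9% at q = 50%. Those events carry no independent information on the association.
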